### Treatment pathways following intervention

In the urodynamics plus comprehensive clinical assessment arm the treatment pathway is guided by the urodynamics diagnosis and is in line with the NICE guideline (CG171; See Additional file 1 Treatment Pathway A). The latter recommends BoNT-A 200 units as the first treatment; however since its publication, further evidence confirmed the efficacy of BoNT-A treatment at the lower dose of 100 units with less adverse events [35] and it has since been licensed in that dose. Note: Subsequent NG123 also recommended initial treatment with 100 units [13].

NICE CG171 also recommends offering SNM treatment for patients who are unable or unwilling to perform CISC or following unsuccessful BoNT-A treatment pending MDT discussion [11]. However, in view of the lack of robust evidence on the best sequence of treatments in women with refractory OAB, participants in both arms of the FUTURE study can be offered either BoNT-A (100 units) or the SNM test; the decision will be discussed in the local MDT or as per local standard best practice. This approach will vary between units depending on their local clinical practice and the availability of treatments. Participants with other diagnoses on urodynamics would be offered the appropriate treatments.

Depending on the clinical outcome of treatment, we will offer participants with persistent or de novo symptoms urodynamic tests and treatment accordingly or further/ repeat treatment according to comprehensive clinical assessment only.

In the comprehensive clinical assessment only arm, the treatment pathway is guided by the clinical diagnosis and non-invasive tests (See Additional file 1 Treatment Pathways B). Considering the evidence above, we will offer participants with clinically diagnosed refractory OAB or urgency predominant MUI either BoNT-A (100 units) or SNM test. We will discuss the decision in the local MDT or as per local standard best practice. This approach will vary between units depending on their local clinical practice and the availability of treatments. We will offer participants with other clinical diagnoses (such as overflow incontinence or SUI predominant MUI) and other appropriate treatments such as CISC, SUI surgery or other medical/conservative treatments as per local standard best practice.

Depending on the clinical outcome of initial treatment, we will offer participants with persistent or de novo symptoms urodynamics and treatment accordingly or may consider repeat/further treatment according to comprehensive clinical assessment only (e.g. we may offer patients with persistent OAB symptoms following treatment with 100 units of BoNT-A treatment the option of repeat BoNT-A treatment).

Deviation from the treatment pathways may occur depending on the local clinical practice and the availability of treatments in the participating units. However, the Chief Investigator (CI) or delegate will assess patterns of deviations.

### Intervention data to be collected

We will collect intervention data on case report forms (CRFs). For both arms, this includes data from the detailed medical history, clinical examination and 3-day bladder diary, as well as a clinical diagnosis (OAB versus MUI).

For the urodynamics plus comprehensive clinical assessment arm, we will also collect data from the urodynamics test, including urodynamics diagnosis (DO/MUI/USI/others), voiding assessment on free uroflowmetry (voided volume, post-voiding residual urine volume, voiding pattern and maximum and average flow rate), voiding assessment on pressure flow studies (if performed) and maximum urethral closure pressure on urethral pressure profile (if performed).

For the comprehensive clinical assessment arm, we will collect data on the post-voiding residual urine volume using ultrasound bladder scanning (and/or non-invasive free uroflowmetry if performed).

### Criteria for discontinuing or modifying allocated interventions {11b}

There are no special criteria for discontinuing or modifying allocated interventions. However, in both study arms, we will offer participants evidence-based treatments for refractory OAB according to their diagnosis and as per the defined treatment pathways which were developed in line with the NICE guideline CG171 [11].

### Strategies to improve adherence to interventions {11c}

To be assured of good quality measurements and accurate urodynamics data recording, we have developed a “FUTURE study Guide for Urodynamics Best Practice” (Additional file 2) in conformity with the 2016 International Continence Society (ICS) Good Urodynamics Practices [36].

We have developed clear guidance for urodynamic trace marking to standardise the points used for data in each study and make central reading/audit of traces more reliable.

Prior to performing the first randomised urodynamics test within the FUTURE Study, collaborating units are required to
Undertake urodynamics machine calibration checks for measurements, andSubmit two anonymous urodynamics traces with their reports for central reading and review by a panel of experts within the FUTURE study team. Feedback is given to centres for any improvement steps needed.

During the course of the study:
Collaborating units will submit copies of urodynamics traces/reports for all participants that are randomised to the urodynamics arm for archiving as study data.Random central check of traces/reports will be undertaken after ten traces/reports are submitted per unit (five for low recruiting units) by the panel above for quality assurance. If required, one to one feedback will be provided and closer monitoring (random central checks after five traces/reports) undertaken (Additional file 2).

Web-based training on best urodynamics practice is available for collaborating units. An expert clinical engineer (co-investigator) provides one to one support for collaborating units if/when required.

### Relevant concomitant care permitted or prohibited during the trial {11d}

Usual care for participants continues throughout the trial. No relevant concomitant care is prohibited.

### Provisions for post-trial care {30}

Standard care is provided within the UK National Health Service.

### Outcomes {12}

The primary outcome measure is participant-reported success at 15 months post-randomisation (approximately 12 months post-treatment) as measured by the PGI-I.

The PGI-I is a validated single item questionnaire designed to assess the participant’s impression of changes in her urinary symptoms. The PGI-I asks the participant to best describe her urinary symptoms, compared with how they were before the study intervention, on a 7-point scale scored as: (1) “very much improved,” (2) “much improved,” (3) “improved,” (4) “same,” (5) “worse,” (6) “much worse,” or (7) “very much worse. “Success” is defined as responses of “very much improved” or “much improved”; this will capture whether the women are satisfied with their treatment.

The primary economic outcome is the incremental cost per QALY gained of urodynamics and comprehensive clinical assessment compared to comprehensive clinical assessment only, modelled over the lifetime of the patients.

Secondary outcome measures are as follows:
○ A less strict definition of success at 15 months derived from the PGI-I where success is defined as a response of “very much improved”, “much improved”, or “improved”.○ Proportion of women receiving invasive treatment at 6 and 15 months post-randomisation.○ Participant-reported outcomes at 3, 6 and 15 months post-randomisation including:▪ OAB symptoms measured by the International Consultation on Incontinence Questionnaire Overactive Bladder (ICIQ-OAB) and the Urgency Perception Scale (UPS);▪ Urgency and UUI episodes measured using the bladder diary;▪ Other urinary symptoms measured using the 3 domains of the International Consultation on Incontinence Questionnaire Female Lower Urinary Tract Symptoms (ICIQ-FLUTS; filling, voiding and incontinence) and the bladder diary;▪ Generic health-related QoL status measured using general (EQ-5D-5L) and condition specific (International Consultation on Incontinence Questionnaire Lower Urinary Tract Symptoms Quality of Life; ICIQ-LUTSqol) QoL assessment tools.○ Adverse events:▪ All serious adverse events;▪ UTI requiring antibiotic treatment;▪ For subsequent treatments:
○ BoNT-A treatment: urinary retention requiring clinical intervention (e.g. catheterisation); CISC.○ SNM: infection of the SNM lead; lead migration, revision of surgery; wound infection.○ SUI surgery: Bladder injury; intra operative bleeding requiring return to theatre; post-operative wound infection; nerve injury; tape exposure/extrusion into vagina/lower urinary tract; tape excision/division; tape infection; new onset and related pelvic pain; urinary retention requiring intervention (e.g. catheterisation); CISC; others.○ Qualitative study outcomes:▪ Participants’ attitudes to invasive testing and expected outcomes (prior to randomisation or knowing their allocated study group);▪ Participants’ attitudes to potential treatment options (prior to randomisation or knowing their allocated study group);▪ Participants’ experience of urodynamics and opinions regarding treatment outcome to include evaluation of treatment satisfaction or desire for further treatment (3 to 6 months post-treatment);▪ Surgeon attitudes to the influence of urodynamics on decision-making (at start of the study and 6 to12 months after starting recruitment at their sites).○ Secondary economic outcomes include:▪ Incremental cost per QALY gained of urodynamics and comprehensive clinical assessment compared to comprehensive clinical assessment only up to 15 months;▪ Incremental cost per QALY gained of BoNT-A vs SNM as the initial treatment for refractory OAB over the lifetime of patients;▪ Incremental cost per QALY gained of SNM test and BoNT-A treatment according to clinical assessment only compared to treatment guided by urodynamics over the lifetime of patients;▪ Expected value of perfect information and associated partial values over the lifetime of patients.

### Participant timeline {13}

See Fig. 1 for the participants’ timelines through the trial.

### Sample size {14}

A survey of the collaborating units showed that in clinical practice, the majority of women with refractory OAB are initiated on BoNT-A treatment (60–70%) compared to SNM (15–20%) or other/no treatments (10–25%). In addition, Rovner et al. and Chapple et al. both showed a success rate of around 60% in women with refractory OAB without the urodynamics diagnosis of DO [14, 16]. These two studies defined success differently: Chapple et al. assessed patient-reported success at 12 weeks following injection of 100 units BoNT-A and defined success as greatly improved or improved [16]; Rovner et al. used a dose of 300 units and defined success as no UUI episodes recorded in a 7-day diary recorded at 12 weeks post-treatment [14].

We have also established a consensus amongst clinicians and patient and public involvement groups (PPI) that for urodynamics to be worthwhile, it will need to demonstrate a minimum of 10% superiority over comprehensive clinical assessment only. For 90% power and a 5% level of significance, 986 participants (493/group) are needed using a chi-squared test with continuity correction [37, 38], rising to 1096 (or 548/group) to allow for 10% attrition at 15 months post-randomisation.

### Recruitment {15

Local research teams will identify all potentially eligible women at outpatient clinics or waiting lists for urodynamics/outpatient clinics in each recruiting centre. We may also use participant identification centres (PICs) to identify potential patients. Posters within appropriate clinics will provide information about the study. Local procedures at the participating hospitals will vary and the timing and mode of approach to women and the consent process may accommodate both the specific circumstances at each site and the needs of the women.

We will give or send each eligible woman a PIL describing the FUTURE study and they will have the opportunity to discuss the study with her consultant. Women may also receive their local hospital PIL regarding the urodynamics investigation. Women will have the opportunity to discuss all aspects of the proposed research with the local clinical team (consultant/staff at clinics), the research nurse (RN), and if appropriate, general practitioner, family and friends.

Women may make a decision to participate during an initial consultation with their consultant or during a subsequent visit to hospital (e.g. a clinic appointment) or alternatively at home.

The local RN may telephone eligible women to discuss any queries and arrange a baseline assessment visit. For women who decide to participate, we will send or give them the study documents (consent form and baseline questionnaires) to complete at home. They can either send their completed documents (consent form and baseline questionnaire) through the post to the local team at their treating hospital or bring it with them if they are returning to hospital for another consultation or assessment.

We will keep a log of all potentially eligible patients assessed in order to document the reasons for non-inclusion in the study (e.g. reason they were ineligible or declined to participate) to inform the Consolidated Standards of Reporting Trials (CONSORT) diagram. We will record brief details of potentially eligible patients in the screening logs at each site (these are an aid to monitoring potential participant inclusion). We will assign all women who enter the study a unique study number.

We will send participants who also consent to the qualitative research a dedicated PIL for the qualitative study interviews. This will be followed by an email and/or phone call from a qualitative team researcher to answer any of the participants’ queries.

## Assignment of interventions: allocation

### Sequence generation {16a}

Eligible and consenting participants will be randomised after completing the baseline assessment to either “urodynamics and comprehensive clinical assessment” or “comprehensive clinical assessment only” using the randomisation application at the trial office at the Centre for Healthcare Randomised Trials (CHaRT), University of Aberdeen.

This randomisation application is available 24 h a day, 7 days a week as a web-based application. The randomisation uses stratified random permuted blocks with (a) centre, and (b) diagnosis of OAB versus Mixed Urinary Incontinence used as stratum. In addition, a random component is used in the minimisation algorithm to ensure concealment of the allocation.

### Concealment mechanism {16b}

The web-based randomisation system ensures allocation concealment.

### Implementation {16c}

The Principal Investigator (PI) at site, or member of the local research team (with delegated authority), will access the web-based system. They will enter stratification characteristics into the web-based system, which returns the allocation status. We will inform participants of their allocated pathway following randomisation. If the participants are not present at the time of randomisation, the research team will contact the participant to inform them of the allocated pathway after randomisation. We will inform participants who have consented to take part in the embedded qualitative study of their allocated pathway after their initial qualitative interview.

## Assignment of interventions: Blinding

### Who will be blinded {17a}

Participants, clinical staff or the central trial team cannot be blinded to the allocated procedure because of the nature of the interventions.

### Procedure for unblinding if needed {17b}

There are no requirements for emergency unblinding procedures.

## Data collection and management

### Plans for assessment and collection of outcomes {18a}

We will collect data at baseline and at 3, 6 and 15 months post-randomisation (see Table 1). We will also collect intervention data for each participant.

**Table 1 Tab1:** Source and timing of outcome measures to be assessed

Outcome measure	Source	Timing			
		Baseline^**a**^	Post-randomisation (months)		
			3	6	15
Treatment success PGI-I	PQ		✓	✓	✓
Generic health status	PQ	✓	✓	✓	✓
EQ-5D-5L					
Condition specific quality of life	PQ	✓		✓	✓
ICIQ-LUTSqol					
Urinary symptoms	PQ	✓	✓	✓	✓
ICIQ-OAB					
ICIQ-FLUTS					
UPS: Urgency Perception Scale					
Urgency and urgency urinary incontinence episodes on (3-day bladder diary)	PQ	✓		✓	✓
Bladder scan	CRF	✓			
Interventions received	CRF, PQ		✓	✓	✓
Adverse events	CRF, PQ		✓	✓	✓
NHS primary and secondary healthcare use	CRF, PQ	✓		✓	✓
Participant resource use	PQ	✓		✓	✓

*CRF* case report form, *PQ* participant-completed questionnaire

^a^Baseline is after informed consent has been given but prior to randomisation

We will collect qualitative data via face to face participants’ interviews where possible, with telephone interviews included for remote study sites, and carried out by an experienced qualitative researcher.

### Plans to promote participant retention and complete follow-up {18b}

We offer and use all methods of delivery and collection of questionnaires and reminders including use of research teams for time points associated with hospitalisation, post, e-mail, web-based and SMS text, taking into account each participant’s stated preferred means of receiving and completing the measures (recorded on the participant contact preference form).

We will send up to three reminders to participants by post, email, phone or text message, taking into account any preferences they may have for mode of communication.

We will send a small token of appreciation (gift voucher(s) of modest value up to £15) to participants on receiving their completed follow-up questionnaires, unless they opt out on the study consent form.

### Data management {19}

The local research team enters locally collected data in the centres. Staff in the trial office will work closely with local research teams to ensure the data are as complete and accurate as possible.

Follow-up questionnaires to participants are sent from and returned to the trial office in Aberdeen. Extensive range and consistency checks are designed to further enhance the quality of the data.

### Confidentiality {27}

Data collected during the course of the research is kept strictly confidential and accessed only by members of the trial team and may be looked at by individuals from the Sponsor organisation or NHS site for the purposes of monitoring and audit.

Participants are allocated a unique study number. Participant’s details are stored on a secure database under the guidelines of the 1998 Data Protection Act. To comply with the 5th Principle of the Data Protection Act 1998, personal data will not be kept for longer than is required for the purpose for which it has been acquired. The CHaRT senior IT manager (in collaboration with the CI) manages access rights to the data set. We anticipate that anonymised trial data may be shared with other researchers to enable international prospective meta-analyses.

### Plans for collection, laboratory evaluation and storage of biological specimens for genetic or molecular analysis in this trial/future use {33}

There are no plans for the collection, laboratory evaluation or storage of biological specimens for genetic or molecular analysis in this trial.

## Statistical methods

### Statistical methods for primary and secondary outcomes {20a}

We will compare primary and secondary outcomes using generalised linear models, with adjustment for the minimisation covariates (centre and diagnosis of OAB versus MUI). We will use sensitivity analyses to explore additional adjustment of healthcare professional effects which arise from a better diagnosis being made due to the use of urodynamics. This is similar to adjusting for surgeon effects when there is more than one surgeon within a centre.

The primary outcome is participant-reported success as measured by the PGI-I at 15 months post-randomisation (approximately 12 months post-treatment). For the primary analysis, the PGI-I responses will be dichotomised to “success” defined as “very much improved” or “much improved” as this is felt to be the best categorisation of whether the women are satisfied with their treatments and interventions. We will use a repeated measures mixed effects logistic regression, including the 6-month measurement to increase the power to estimate the treatment effect at 15 months post-randomisation.

We will analyse secondary outcomes using the appropriate linear model. For example, we will analyse the less strict definition of success using a repeated measures mixed effects logistic regression in the same way as the primary outcome will be analysed. We will also analyse the proportion of women receiving invasive treatment using a logistic regression. We will analyse continuous outcomes such as the ICIQ-FLUTS scores and quality of life scores and the EQ-5D-5L using a repeated measures mixed effects linear regression.

We will make available the statistical analysis plan and the health economy analysis plan as a separate publication(s).

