### Within trial cost-effectiveness analysis

The within trial analysis will follow the best practice guidelines [40]. The analysis will calculate total costs and QALYs for each patient and estimate the incremental costs and QALYs using a seemingly unrelated regression model with baseline covariates including age and baseline EQ-5D-5L score and missing data imputed using multiple imputation [41, 42].

We will base the cost-effectiveness acceptability curves on the adjusted and imputed analysis described above. We will undertake deterministic sensitivity analyses to look at three sources of methodological uncertainty; societal perspective, the EQ-5D-5L tariff and any QALY loss associated with urodynamics identified in the exploratory analysis described above. Undertaking a sensitivity analysis with the EQ-5D-5L tariff is required as alternative tariffs are available; the current recommended tariff is the van Hout “cross-walk” tariff [43]

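### The outcome list and Table 1 disagree on 3-month bladder diary and ICIQ-LUTSqol data, and the stated covariates for continuous secondary outcomes include no baseline score

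*Protocol article*

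**What the plan says.** **Timing.** Outcomes {12} gives one common schedule, "Participant-reported outcomes at 3, 6 and 15 months post-randomisation including", and lists several instruments under it. Among them are diary-recorded urgency and urgency incontinence episodes, the diary again for other urinary symptoms, and ICIQ-LUTSqol. Table 1, in Plans for assessment and collection of outcomes {18a}, has a row "Urgency and urgency urinary incontinence episodes on (3-day bladder diary" and a row for ICIQ-LUTSqol. Each is ticked at baseline, 6 and 15 months, and the 3-month cell is blank.

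**Covariates.** Statistical methods {20a} says that primary and secondary outcomes will be compared with generalised linear models "with adjustment for the minimisation covariates (centre and diagnosis of OAB versus MUI". For continuous outcomes it then specifies "quality of life scores and the EQ-5D-5L using a repeated measures mixed effects linear regression". It does not say whether the baseline value is a covariate, one of the repeated measures, or neither. The same section defers detail: "We will make available the statistical analysis plan and the health economy analysis plan as a separate publication(s". Within trial cost-effectiveness analysis specifies a "seemingly unrelated regression model with baseline covariates including age and baseline EQ-5D-5L score". Table 1 defines baseline as after consent and before randomisation.

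**The concern.** The outcome list and the collection schedule are core protocol content. If Table 1 is right, the article lists 3-month outcomes that no one can report. If Outcomes {12} is right, the schedule leaves out data that sites and the trial office are expected to collect.

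The second matter is efficiency. A pre-randomisation score on the same instrument is usually among the best predictors of the follow-up score. A model adjusted only for centre and diagnosis gives wider intervals for symptoms and quality of life than the collected data allow, and leaves chance baseline imbalance unadjusted. The article names baseline EQ-5D-5L as a covariate in the economic model but names no baseline value in the clinical analysis of the same instrument.

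**Working it through.** **Timing: the two places side by side**

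| Instrument | Outcomes {12} | Table 1, follow-up |
|---|---|---|
| EQ-5D-5L | 3, 6, 15 months | 3, 6, 15 |
| ICIQ-OAB, ICIQ-FLUTS, UPS | 3, 6, 15 months | 3, 6, 15 |
| ICIQ-LUTSqol | 3, 6, 15 months | 6, 15 |
| Bladder diary | 3, 6, 15 months | 6, 15 |

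The first two rows carry four ticks in Table 1, counting baseline. The last two carry three, with the gap in the 3-month position. That pattern is unlikely to come from a badly extracted table.

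**The plan's own figure.** The only sample size calculation is for the primary outcome: 493 per group, 90% power, 5% level (taken as two-sided), continuity-corrected chi-squared test. I take 60% against 70% from the Sample size section.

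- Uncorrected: n = [1.960·√(2·0.65·0.35) + 1.282·√(0.60·0.40 + 0.70·0.30)]² / 0.10² ≈ 476.01, rounded up to 477.
- Corrected: (476/4)·[1 + √(1 + 4/(476·0.10))]² ≈ 496, against 493 stated (0.6% apart).
- Attrition: 493/0.9 = 548 and 986/0.9 = 1096, as stated.

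The figure reproduces. The article makes no power claim for any continuous secondary outcome.

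**Value of the baseline score.** Let r be the correlation between the baseline and follow-up values of one instrument. The article gives none, so r is assumed over 0.3 to 0.7. With baseline as a covariate, the variance of the arm difference at one follow-up time is multiplied by 1 − r² and its standard error by √(1 − r²), relative to a model without baseline. With 493 analysed per group, the detectable standardised difference without baseline is (1.960 + 1.282)·√(2/493) = 0.206. With baseline it is 0.206·√(1 − r²), and the equivalent number per group is 493/(1 − r²).

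| r (assumed) | 1 − r² | SE reduction | Detectable difference | Equivalent n per group |
|---|---|---|---|---|
| 0.3 | 0.91 | 4.6% | 0.197 | 542 |
| 0.4 | 0.84 | 8.3% | 0.189 | 587 |
| 0.5 | 0.75 | 13.4% | 0.179 | 657 |
| 0.6 | 0.64 | 20.0% | 0.165 | 770 |
| 0.7 | 0.51 | 28.6% | 0.147 | 967 |

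**Does a repeated measures model secure this gain anyway?** It depends on how baseline enters.

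- As a first occasion with arm means left free at baseline, the complete-data contrast at 15 months is still the raw difference: factor 1, no gain.
- As a change from baseline, the factor is 2(1 − r): 1.20, 1.00 and 0.80 at r = 0.4, 0.5 and 0.6, against 0.84, 0.75 and 0.64 for covariate adjustment.
- As a covariate, or in a model that constrains the arms to a common baseline mean, the gain is obtained.

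Naming a repeated measures model therefore does not settle the matter.

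**The case against.** **On covariates.** The sentence in {20a} is general: it covers primary and secondary outcomes together and does not say that nothing else will be included. Outcome-specific covariates are ordinary SAP content, and the article points to a separate SAP. The economic regression is a different analysis with its own plan. QALYs are interpolated between EQ-5D-5L time points, so baseline EQ-5D-5L is a natural covariate there, and its presence does not show that the clinical model lacks it. Table 1 lists collection times, not covariates, so it does not conflict with {20a}. All of this stands. A reader might infer that the plan leaves baseline out and so loses precision. The text supports only that no baseline score is named.

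**On timing.** A single umbrella heading over several instruments is a likely cause. The row-by-row schedule is published in the same article. Because 15 months is described as about 12 months after treatment, 3 months falls around the time of treatment, so little may hang on these results. That limits the consequence but does not remove the contradiction. A reader might infer that the 3-month data are never collected, or that their absence from the results would signal selective reporting. The article supports neither: Table 1 may be the part in error, and the schedule is in plain view.

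**Conclusion.** The timing conflict is established by direct reading and needs no assumption. Two instruments have a 3-month assessment in the outcome list and none in the schedule, and the article does not settle which is correct. On its own this warrants a correction.

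The baseline point holds in a conditional form. The stated covariates are centre and diagnosis, and the role of the collected baseline scores is not given. If the SAP also leaves them out, the standard errors for continuous secondary outcomes at a single follow-up time could be about 5% to 29% smaller with adjustment. That range rests on assumed correlations of 0.3 to 0.7, 493 analysed per group for the detectable differences and equivalent numbers, and comparison with a model that makes no use of baseline. The randomised comparison is unbiased either way. The primary outcome and its sample size are unaffected, since PGI-I has no baseline value.

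**What to change.** 1. Reconcile Outcomes {12} with Table 1. Either restrict the bladder diary outcomes and ICIQ-LUTSqol to 6 and 15 months, keeping 3, 6 and 15 months for the other instruments, or add the 3-month ticks to Table 1 if the 3-month questionnaire contains them. The trial team can settle this by looking at that questionnaire. The cost is one corrected line.

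2. Unless the SAP already does so, state that each continuous secondary outcome is analysed with its own baseline value as a covariate beside centre and diagnosis, or by a constrained longitudinal model. Add a simple rule for missing baseline values, such as mean imputation. The cost is a line or two in the SAP, with no new data.

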### Methods in analysis to handle protocol non-adherence and any statistical methods to handle missing data {20c}

Analysis will be by intention-to-treat. We will assess how robust all findings are to any missing data (anticipated to be no more than 10% for the primary outcome) using multiple imputation approaches under an assumption of missing at random. We will consider non-ignorable missing data mechanisms if the patterns of missing data across the two randomised groups suggest this is appropriate.

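### The primary PGI-I model is valid but leaves out baseline severity and age, forgoing a modest efficiency gain from data already collected

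*Protocol article*

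**What the plan says.** Section {20a} of the Protocol article gives one adjustment set for primary and secondary outcomes: "with adjustment for the minimisation covariates (centre and diagnosis of OAB versus MUI". The primary outcome is PGI-I dichotomised to success or not. The section describes the model as follows, with time counted in months: "We will use a repeated measures mixed effects logistic regression, including the 6-month measurement to increase the power to estimate the treatment effect at 15". The only further adjustment it names is a sensitivity analysis: "We will use sensitivity analyses to explore additional adjustment of healthcare professional effects". A separate statistical analysis plan is announced and is not shown.

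Table 1, in section {18a}, has no baseline PGI-I. It does schedule ICIQ-OAB, ICIQ-FLUTS, UPS, ICIQ-LUTSqol and EQ-5D-5L at baseline, which its footnote places before randomisation. The same holds for the diary row: "Urgency and urgency urinary incontinence episodes on (3-day bladder diary".

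The within-trial economic regression uses "baseline covariates including age and baseline EQ-5D-5L score". For missing outcomes, section {20c} plans a robustness check by "multiple imputation approaches under an assumption of missing at random", and non-ignorable mechanisms if the pattern of missing data calls for them.

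**The concern.** When a follow-up measure has a baseline counterpart, adjusting for that baseline is routine and brings in much of the prognostic information. PGI-I has no such counterpart. Unless another baseline score is put into the model, entry severity is absent from the analysis of the deciding outcome, even though it has been measured.

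The plan accepts the reasoning elsewhere. It brings in the 6-month PGI-I expressly to gain power, and it adjusts the economic regression for age and a baseline score. In a logistic model, adding a prognostic baseline covariate raises the expected test statistic for treatment. Leaving it out gives up some power on the main superiority test. The question is how much.

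**Working it through.** **1. The plan's own sample size.** The Sample size section {14} states: "For 90% power and a 5% level of significance, 986 participants (493/group) are needed using a chi-squared test with continuity correction". The control rate comes from two cited trials that "both showed a success rate of around 60% in women with refractory OAB without the urodynamics diagnosis of DO", and the target difference is 10 points, so the comparison is 60% v 70%. I assume a two-sided test.

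- Unpooled formula: n = (1.960 + 1.282)² × (0.6×0.4 + 0.7×0.3) / 0.1² = 472.8 per group.
- Continuity correction: n/4 × [1 + √(1 + 4/(n×0.1))]² = 492.6, so 493 per group and 986 in total, as stated. The pooled-variance version gives 496 per group (992), within 1%.
- Attrition: 986/0.9 = 1095.6, so 1096, as stated.

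This calculation counts on no gain from covariates.

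**2. Power without a severity covariate (logistic Wald test, 493 per group).**

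- Log odds ratio: ln(0.7/0.3) − ln(0.6/0.4) = 0.8473 − 0.4055 = 0.4418.
- SE = √[1/(493×0.24) + 1/(493×0.21)] = √0.01811 = 0.1346.
- z = 3.283, and power = Φ(3.283 − 1.960) = 90.7%.

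**3. Power with a baseline score added.** The model is logit P(success) = a + θ·arm + β·x, with x a standard normal score standing for severity and age combined. For each β, the intercepts are solved so that the marginal rates stay at 60% and 70%, and θ is their difference. The SE comes from the inverse of the expected information, the sum over arms of 493 × E[p(1−p) r r′] with r = (1, arm, x). Power is Φ(θ/SE − 1.960). The equivalent gain in participants is (z/3.283)² − 1. The documents do not give β, so a range is assumed.

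| Assumed OR per SD | θ | SE | z | Power | Gain (points) | Equivalent extra participants |
|---|---|---|---|---|---|---|
| 1.0 | 0.4418 | 0.1346 | 3.283 | 90.7% | 0 | 0 |
| 1.2 | 0.4451 | 0.1351 | 3.295 | 90.9% | 0.2 | 1% |
| 1.35 | 0.4507 | 0.1360 | 3.315 | 91.2% | 0.5 | 2% |
| 1.65 | 0.4659 | 0.1383 | 3.368 | 92.0% | 1.3 | 5% |
| 2.0 | 0.4863 | 0.1414 | 3.438 | 93.0% | 2.3 | 10% |
| 2.72 (extreme) | 0.5287 | 0.1477 | 3.579 | 94.7% | 4.0 | 19% |

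These figures use the 15-month response alone and ignore centre. The 6-month PGI-I will carry some of the same prognostic information, so the gain in the planned model would be smaller.

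**4. Missing outcomes.** Suppose 10% are missing and the omitted score (OR 1.35 to 2.0 per SD) also drives missingness, with a log odds of 0.5 per SD. If that dependence is the same in both arms, the expected complete-case difference moves by 0.05 to 0.10 points from the true 10. If it runs in opposite directions by arm (+0.5 v −0.5), it moves by 0.6 to 1.4 points. Both figures ignore the 6-month PGI-I and any baseline variables in the imputation model.

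**The case against.** The strongest reply is that adjusting for the randomisation factors is a standard and valid primary analysis, that section {20a} never says these are the only covariates, and that further covariates are often settled in the analysis plan, which is not shown. This stands to the extent that the protocol contains no error or contradiction here. It does not remove the suggestion, because the section does state an adjustment set and the proposal changes that stated method.

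The gain is also of unknown size. PGI-I asks each woman to compare herself with her own earlier state, so strong prognostic value of entry severity cannot be presumed. This stands, and is why the result is given as a range.

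A reader might draw three stronger conclusions that the documents do not support.

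- *That the trial is underpowered without these covariates.* The sample size rests on an unadjusted test and is met without them.
- *That the estimate is biased toward the null.* The smaller odds ratio without the covariate reflects non-collapsibility: it answers a slightly different question and is not biased. A woman-level random effect, which the planned model implies, already makes the odds ratio conditional, so the simple attenuation argument does not carry over directly.
- *That the missing-data handling is unsound.* Women with a 6-month PGI-I still inform the 15-month estimate, and section {20c} plans multiple imputation, whose model may include baseline severity. Material bias needs dropout to depend on severity in opposite directions by arm, and the documents give no reason to expect that. Conditioning on severity would at most make missing-at-random somewhat more plausible for women with no follow-up PGI-I.

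Nor does the economic regression show an inconsistency. Baseline EQ-5D-5L enters the QALY calculation arithmetically, whereas PGI-I has no baseline value.

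**Conclusion.** The point holds as a low-cost improvement in efficiency. The stated model is valid and meets its planned power, but it leaves unused the severity data collected before randomisation. At 493 per group and 60% v 70%, the forgone gain is about 0.2 to 2.3 power points, equal to about 1% to 10% more participants (roughly 7 to 96 of 986). This rests on an assumed odds ratio of 1.2 to 2.0 per standard deviation, and the gain would be smaller with the 6-month PGI-I in the model. If severity and age are not prognostic, almost nothing is gained or lost.

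**What to change.** In section {20a} and the analysis plan, name baseline ICIQ-OAB score and age as fixed covariates in the primary mixed-effects logistic model, alongside centre and diagnosis. Fix the choice before any comparison by arm. Fill missing baseline values by a simple method that does not use arm. State that the reported odds ratio is conditional on these covariates, and report the centre-and-diagnosis model as a sensitivity analysis.

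The cost is a few sentences and no new data. The one drawback is that the two models' odds ratios will differ slightly because they condition on different variables, so both should be shown and the difference explained.
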